## Abstract

**Abstract:**

Nonrestorative sleep (NRS) is one of the cardinal symptoms of insomnia and can occur independent of other components of insomnia. Among the sleep disturbances, NRS has been little studied in the general population, even though this symptom plays an important role in several medical conditions associated with chronic inflammation such as heart disease, fibromyalgia, and chronic fatigue syndrome, as well as various sleep disorders. There is paucity in the literature about effective treatments for NRS. Ashwagandha (*Withania somnifera*) has been demonstrated to reduce anxiety and stress, allowing the body to settle down and prepare for sleep. This study will be a double-blind, randomized, placebo-controlled interventional study in NRS population.

The NRS participants are identified using Restorative Sleep Questionnaire-weekly version (RSQ-W) questionnaire. Actigraphy and polysomnography are used for the objective assessment of sleep. The other assessments used are Hamilton Anxiety Depression Scale (HADS), World Health Organization Quality of Life (WHOQOL) scales, and C-reactive protein. Routine blood and urine analyses will be conducted to assess the safety of treatment. Duration of study for each participant will be 50 days with “day one” for screening followed by randomization for the treatment. The duration for medicine/placebo intake shall be 42 days.

Primary outcome will be to evaluate effect of daily supplement of ashwagandha extract compared with placebo in subjects with NRS at 6 weeks from baseline, as assessed by the total score of RSQ-W.

**CTRI Registration Number::**

CTRI/2017/02/007801

## Introduction

1

Disturbed sleep is one the commonest encounters of day-to-day life in the fast moving society.^[1,2]^ Most common sleep disturbances are “difficulty in initiating sleep” and “nonrestorative sleep” (NRS). This results in daytime fatigue. In a Swedish survey of 1550 randomly selected subjects from entire Swedish population, almost one-third felt the need for the treatment and yet had not consulted healthcare provider.^[3]^ Insomnia symptoms are highly heterogeneous in terms of causes and manifestations. Recent studies have suggested that NRS symptoms may or may not be present along with insomnia symptoms such as difficulty in initiating and/or maintaining sleep (DIS and/or DMS). Thus, sleep disorders may be grouped as pure DIS and/or DMS, only NRS, and combination of DIS and/or DMS with NRS.^[4]^

NRS can be defined as a moderate to severe complaint of being unrefreshed upon awakening (even if the sleep duration is sufficient according to the subject) occurring at least 3 nights per week during a period of at least 1 month.^[5]^ NRS has been little studied in the general population even though it influences several medical conditions such as heart disease, fibromyalgia, and chronic fatigue syndrome, as well as various sleep disorders. When compared with subjects who have only DIS/DMS, subjects with NRS reported more frequently a variety of daytime impairment (irritability, physical, and mental fatigue) and consulted a physician twice as frequently for their sleeping difficulties.^[5]^ According to International Classification of Sleep Disorders (ICSD), NRS is an associated feature in many intrinsic sleep disorders such as sleep- related breathing disorders and Parasomnias.^[6]^ Other conditions, such as chronic fatigue syndrome and depression, have increased peripheral inflammatory markers and NRS as common features.^[7]^ This underscores the causative relationship between systemic inflammation and NRS.

Currently available treatments for insomnia, including pharmacologic managements and psychological therapy, are designed for DIS and/or DMS rather than NRS, even though NRS is associated with a greater level of functional impairment.^[8]^ Despite recent advances in the development of newer hypnotics in modern medicine, a significant proportion of subjects with sleep disturbances, both locally and internationally, consume herbal hypnotic regularly.^[9]^ Therefore, there is always a search for a candidate molecule for the better management of NRS.

Given the multifactorial involvement in NRS, it seems logical that a medicine that would cause reduction in stress, has antidepressant property, reduces peripheral inflammatory activity, and also help in improving physical performance will be useful in treating NRS.

In multiple clinical trials, Ashwagandha (*Withania somnifera*) has shown to be effective in reduction of chronic inflammation markers such as C-reactive protein (CRP).^[10]^ It was shown to have mild anti-anxiety and anti-depressant effect and effective in reducing postchemotherapy fatigue in breast cancer subjects.^[10–14]^ Thus, Ashwagandha would very likely have an impact on “NRS.” The investigational product studied in this clinical study is an extract of Ashwagandha (*W somnifera*) developed by M/s Arjuna Natural Extracts Ltd., Aluva, Kerala, India, that is standardized to contain about 35% glycowithanolides.

## Methods

2

### Study objectives

2.1

The primary objective of this trial will be to evaluate the effect of daily supplementation of Ashwagandha extract compared with placebo in subjects with NRS at 6 weeks from baseline, as assessed by the total score of Restorative Sleep Questionnaire-weekly version (RSQ-W).

The secondary objective will be to compare Ashwagandha and placebo groups on change from baseline up to 6 weeks by actigraphy parameters [average number of awakenings per hour of sleep, average total sleep time (TST) in 1 week, sleep efficiency], nocturnal polysomnogram parameters (only in a subset of 30 subjects) such as sleep onset latency (SOL), wakefulness after sleep onset (WASO), TST, Micro-arousal index and time spent in individual sleep stage, quality of life scores using WHOQOL-BREF scale, depression, and anxiety scores using Hospital Anxiety and Depression Scale and CRP levels.

### Study rationale

2.2

NRS (with or without DIS and/or DMS) is strongly associated with stress, anxiety, depression, daytime fatigue, and increased CRP. Ashwagandha was shown to be effective in relieving stress and depression. It is also effective in reducing fatigue and inflammatory markers such as CRP levels. Thus, it is proposed that Ashwagandha would likely be effective in reducing NRS.

### Study design

2.3

This is a prospective, randomized, double-blind, parallel, placebo-controlled, single-center, clinical study. The study will be conducted at International Institute of Sleep Sciences, Thane, Maharashtra, India. The study protocol (AN-02ASH 0816H3-IIS01 version. 01 dated October 18, 2016) is approved by institutional ethics committees and registered with Clinical Trials Registry- India (www.ctri.nic.in) (CTRI registration number: CTRI/2017/02/007801). The study will be conducted according to the Declaration of Helsinki 2013, the ICH-GCP E6 (R1, R2) 1996, and ICMR-National Ethical Guidelines for Biomedical and Health Research, 2006. The investigational product will be Ashwagandha extract 300 mg in size “0” capsule of M/s Arjuna Natural Extracts Ltd., Aluva, Kerala, India, and matching placebo in size “0” capsule for reference group.

A total of 150 subjects will be enrolled in this clinical trial to compare the efficacy and safety of the test versus reference product. Study duration per subject will be 6 weeks. Block-randomization will be performed by the statistician using a computer-generated program with blocks of varying length. The length of blocks will be unknown to study team except the statistician involved in generating the randomization list. The mechanism of implementation of the allocation sequence will be sealed envelope method. Opaque sealed envelopes are prepared based on the randomization list. Each envelope will be opened in sequence just before the randomization of a subject and will be kept under controlled access of statistician. The principal investigator (PI) will take the informed consent before enrolling the subjects and will take all necessary precautions in protecting the confidentiality of the subjects. The subjects will be identified throughout and after the completion of the study only by the allotted randomization number to protect the confidentiality. The PI delegated pharmacist will dispense the study products. As this study is double blinded, the PI and the subject will be blinded toward the interventions. If a need to know arises in which case knowing the identity of interventions is necessary, the PI will be permitted to unblind the subject. Adequate subject enrollment would be achieved by those visiting the site, educational pamphlets, and by study camps conducted in nearby places. The enrolled subjects would be assigned to either of the 2 study groups (75 in each study group). Subjects will be instructed to take 2 capsules of Ashwagandha extract 300 mg or matching placebo once daily in the evening 2 hours before food with water.

### Sample size

2.4

Differences of 10 points and 15 points for RSQ-W total score are considered as clinically significant and clinically highly significant, respectively. Assuming standard deviation of 25 points, these differences correspond to standardize effect size of 0.4 (small-to-medium) and 0.6 (medium-to-large), respectively, as per Cohen recommendation. The difference of 10 points for RSQ-W total score (range 0–100 points) also translates to about 1-point change on 5-point Likert scale in 4 of 9 items of the RSQ-W. Similarly, the difference of 15 points for RSQ-W total score translates to about 1-point change in 5 of 9 items of the RSQ-W.

Group-sequential method will be used to determine the sample size. The planned sample size of 150 subjects (75 in each study treatment group) will be required to detect a difference of 10 points in change in RSQ-W total score at 6 weeks from the baseline between the study treatment groups, assuming a standard deviation of 25 points and a 15% drop-out rate, to achieve 80% statistical power at 5% (2-sided) level of significance. Two interim analyses are planned to occur after completion of the study of 50 subjects and 150 subjects. If the analysis turns out to have a statistically nonsignificant difference, then the enrollment may extend to 236 subjects. The final analysis will be performed when all 236 subjects complete the study.

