### Description of any interim analyses and stopping guidelines

2.9

Interim analyses for efficacy are planned after 50 and 150 subjects complete the 6-week assessment for the primary outcome (or discontinue the study) using a critical *P* value of ≤.0002 for the first analysis and ≤.012 for the second analysis. These boundaries are obtained using O’Brien–Fleming spending function and based on an overall significance level of 5%. That is, the study is likely to be stopped for strong efficacy signal at the first and second interim analysis if the observed mean difference between the study treatment groups is at least 26 points and 12 points, respectively (assuming SD = 25 points, and drop-out rate = 15%). The study may also be stopped due to futility at any interim analyses on discretion of the DMC. If we do not get a desired statistical difference with the analysis of 150 subjects, then we will continue the enrollment up to 236 subjects and the final analysis will be performed when all 236 subjects complete the study, using a critical *P* value of ≤.0475.

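### The 80% power claimed for 150 subjects belongs to the 236-subject maximum; at 150 power is about 61% at the 5% level and about 40% at that look's own critical value

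*Protocol article*

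**What the plan says.** The Sample size section (2.4) states: "The planned sample size of 150 subjects (75 in each study treatment group) will be required to detect a difference of 10 points" in the change in RSQ-W total score at 6 weeks, "assuming a standard deviation of 25 points and a 15% drop-out rate, to achieve 80% statistical power at 5% (2-sided) level of significance". The same section then makes the analysis at 150 the second of two interim analyses and adds that, after a non-significant result, "then the enrollment may extend to 236 subjects". The final analysis is placed at 236.

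The section on interim analyses and stopping guidelines (2.9) sets critical P values of .0002 at 50 subjects, .012 at 150 and .0475 at 236. There the extension is not optional: "then we will continue the enrollment up to 236 subjects". The DMC may also stop for futility at its discretion.

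Study design (2.3) says: "A total of 150 subjects will be enrolled in this clinical trial", with 75 per group. Population (2.6) repeats 150 as the total.

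**The concern.** The sentence in 2.4 gives every input needed to fix the sample size, and the result does not follow from them. It presents 150 as the size that delivers 80% power, yet the same paragraph treats 150 as an interim look, which 2.9 tests at a much stricter level than 5%.

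The text disagrees with itself on whether the trial goes on after a non-significant result at 150, and two other sections give 150 as the whole trial. If recruitment ended there, a negative result would be reported as coming from a trial with 80% power for the difference that the protocol calls clinically significant. In fact, under its own boundary, the trial would have been more likely to miss that difference than to find it. The Discussion says that a negative result would be important for later work, so the power behind such a result has to be stated correctly.

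**Working it through.** **Inputs.** Difference 10 points, SD 25, two-sided 5%, 80% power, 15% drop-out, 1:1 allocation (2.4). Looks at 50, 150 and 236 with critical P .0002, .012 and .0475 (2.9).

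**1. Sample size from the stated inputs.** n per arm = 2 × (z₀.₉₇₅ + z₀.₈₀)² × SD² / difference² = 2 × (1.960 + 0.842)² × 625 / 100 = 98.1, so 99. The t-test needs 100.
- Normal approximation: 198 / 0.85 = 232.9, so 233 (234 for equal arms).
- t-test: 200 / 0.85 = 235.3, so 236.

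The plan's 236 is reproduced and its 150 is not. The protocol does not say how 236 was derived, but the t-test calculation returns it exactly.

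**2. Power at 150.** Evaluable per arm = 75 × 0.85 = 63.75. The standard error of the difference is 25 × √(2/63.75) = 4.428, and 10 / 4.428 = 2.258.
- At .05: Φ(2.258 − 1.960) = Φ(0.298) = 61.7%; noncentral t 61.1%.
- At .012: Φ(2.258 − 2.512) = Φ(−0.254) = 40.0%; noncentral t 38.9%.
- With no drop-out (75 per arm), at .05: 68.8%; noncentral t 68.2%.

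**3. What 150 could detect.** For 80% power at .05 with 63.75 per arm, the difference must be 2.802 × 4.428 = 12.4 points. If the difference stays at 10, the SD must be about 20.2.

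**4. Power at 236.** Evaluable per arm = 118 × 0.85 = 100.3. The standard error is 25 × √(2/100.3) = 3.530, and 10 / 3.530 = 2.833. At .0475: Φ(2.833 − 1.982) = 80.3%; noncentral t 79.9%.

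**5. The three-look design.** Simulation with 2 million runs, the stated boundaries and 15% drop-out:

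| Look | Critical P | Cumulative power, 10 points |
|---|---|---|
| 50 | .0002 | 0.8% |
| 150 | .012 | 40.1% |
| 236 | .0475 | 80.7% |

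**6. A check inside the document.** Section 2.9 says that stopping at the second look needs an observed difference of at least 12 points. If the true difference is 10, the observed one reaches 12 less than half the time: (12 − 10) / 4.428 = 0.452, a chance of about 33%. Recomputing the threshold gives 2.512 × 4.428 = 11.1 points, still above 10. On either figure, power at 150 under the plan's own rule is below 50%.

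**7. Other readings that might rescue 150.**
- One-sided 5% with 15% drop-out gives 73.0%.
- One-sided 5% with no drop-out gives 78.9%, but this contradicts two inputs in the same sentence.
- Adjustment for baseline would need a correlation of about 0.6 (80.6%), and none is stated.
- For a 15-point difference, power at 150 and .012 is 80.9%. That may be where 150 came from, but the text ties the 80% to 10 points.

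**The case against.** The strongest reply is that the design has the power it claims. Section 2.4 says the size comes from a group-sequential method, calls the look at 150 an interim analysis and places the final analysis at 236. Section 2.9, which sets the stopping rules, says that enrolment continues. On that view the optional wording in 2.4 is only loose phrasing for something that depends on an interim result. Low power at an early O'Brien–Fleming-type look is also normal, so 40% at 150 is not a fault in itself.

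Much of this stands: the maximum, the number of looks and the boundaries need no change on this account, and 40% is simply how such a boundary behaves. It does not rescue the power sentence, which names 150 as the required size. Nor does it remove the conflict between 2.4 and 2.9, or the enrolment totals in 2.3 and 2.6.

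A second objection concerns ending at 150 with a 5% test. That does not fit 2.9 as written, which fixes .012 at that look. If .05 were used at 150 while continuation to 236 at .0475 stayed open, overall type I error would be about 7.6%. This is right as a caution. If 150 were truly the final analysis, a .0002 look at 50 followed by a 5% test would keep type I error at about 5.0%, but the boundary would have to be rewritten before that look.

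**Conclusion.** The concern holds. The stated 80% is attached to the wrong sample size: on the protocol's own assumptions it belongs to 236. At 150, power for 10 points is about 61% at the 5% level, roughly 19 percentage points short, and 39–40% at the critical value assigned to that look, roughly 40 points short.

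These figures assume SD 25, drop-out of exactly 15% split equally between arms, and an unadjusted two-group comparison of change scores. The t and normal calculations agree to within about one percentage point. This must be corrected, because it is the primary power statement and the wording of 2.4 can be read as allowing the trial to end at the underpowered size.

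**What to change.** - In 2.3, 2.4 and 2.6, give the planned maximum as 236 subjects (118 per arm), with about 80% power for a 10-point difference. Describe 150 as the second interim look, with about a 40% chance of crossing the efficacy boundary by then if the true difference is 10 points.
- In 2.4, replace the optional extension with the rule already implied by 2.9: enrolment continues to 236 unless the efficacy boundary is crossed or the DMC recommends stopping.
- If the sponsor prefers to end at 150, state the power as about 61% at a 5% test. In that case, rewrite the critical values in 2.9 before the look at 150 and remove continuation to 236.

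The cost of the main correction is wording. It needs no subjects beyond the 236 already foreseen and no change to the boundaries. The full protocol and the registry entry are not at hand; they should be checked for the same statement and corrected if they carry it. The power stated for 150 becomes less favourable, which is the purpose of the correction.

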### Type, sequence, and duration of study periods

2.5

This will be a parallel arm treatment study and all the enrolled subjects will be instructed to take study medication for a treatment period of 6 weeks. There will be a total of 8 to 9 visits and/or follow ups: screening, randomization (visit 1, baseline or day 0), follow-up (visit 2 or day 1), follow-up (visit 3 or day 8), follow-up (visit 4 or day 15), follow-up (visit 5 or day 22), follow-up (visit 6 or day 29), follow-up (visit 7 or day 36), follow-up (visit 8 or day 43), and end of study visit (visit 9 or day 50). Laboratory investigation of all the efficacy and safety parameters will be conducted screening and end of the study. Visits 1,3,7,8, and 9 are mandatory for physical presence at investigation site. Visits 4, 5, and 6 can be done via telephone as per subject's convenience. Visit 2 is only for subjects who will be undergoing polysomnography evaluation.

### Population

2.6

A total of 150 subjects either male or female with age 18 to 65 years will be enrolled in this study. The study eligibility criteria were chosen to maximize generalizability of the results, while taking into account safety and well-being of the participants. The inclusion and exclusion criteria are summarized in Table 1.^[15]^

**Table 1 T1:**
[figure not shown]
Inclusion and exclusion criteria.

### Investigational product and dosage

2.7

The investigational product used in this study is a proprietary detoxified root extract of Ashwagandha (*W somnifera*, Solanaceae) and is manufactured by Arjuna Natural Extracts Ltd, Aluva, Kerala, India. Harvested dried roots of Ashwagandha, visually identified by a qualified botanist, are used to manufacture the extract. The extraction solvent used was ethanol: water with a proportion of 70:30 with a raw material to extract ratio of 13:1. The extract was standardized by HPLC to contain 35% glycowithanolides. The analysis of heavy metals was done with ICP-MS and conforms to EU standards (Lead < 0.5 ppm, Arsenic < 1 ppm, Cadmium < 1 ppm, Mercury < 1 ppm). The microbial assay was done using AOAC, BAM method and conforms to EU standards (Yeast/Mould <100 cfu/g, Salmonella Absent/25 g, *Escherichia coli* Absent/10 g). Identically colored and similar sized placebo capsules were used as the placebo.

Ashwagandha extract or matching placebo capsules will be given as two 300 mg capsules once daily in the evening 2 hours before food with water. The dosage of Ashwagandha extract (Shoden) capsules is standardized to contain 21 mg of glycowithanolides per dose. No dose modification will be allowed in the study. Subjects needing concomitant medication will be managed as per the exclusion criteria of the study. Those subjects having adverse events (AEs) that require standard treatments will be discontinued. Investigational product accountability and telephonic follow-up are used to monitor adherence to protocol.

### Data monitoring

2.8

A Data Monitoring Committee (DMC) will review the safety of the study and the results of the interim analyses and make appropriate recommendations to the trial steering committee. The DMC will be independent from the sponsor and do not have any competing interests. The members have experience in reviewing clinical trial data and have statistical analysis background. Requests for granting public access to the full protocol, participant-level dataset, and statistical code will be as per the SOP of the DMC, which can be sourced with a detailed request to the committee.

### Description of any interim analyses and stopping guidelines

2.9

Interim analyses for efficacy are planned after 50 and 150 subjects complete the 6-week assessment for the primary outcome (or discontinue the study) using a critical *P* value of ≤.0002 for the first analysis and ≤.012 for the second analysis. These boundaries are obtained using O’Brien–Fleming spending function and based on an overall significance level of 5%. That is, the study is likely to be stopped for strong efficacy signal at the first and second interim analysis if the observed mean difference between the study treatment groups is at least 26 points and 12 points, respectively (assuming SD = 25 points, and drop-out rate = 15%). The study may also be stopped due to futility at any interim analyses on discretion of the DMC. If we do not get a desired statistical difference with the analysis of 150 subjects, then we will continue the enrollment up to 236 subjects and the final analysis will be performed when all 236 subjects complete the study, using a critical *P* value of ≤.0475.

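### The critical P values .0002, .012 and .0475 are not O'Brien–Fleming spending boundaries for looks at 50, 150 and 236 subjects, and together they spend 5.16%, not 5%

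*Protocol article*

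**What the plan says.** Section 2.9 of the protocol article fixes the timing of the interim looks: "Interim analyses for efficacy are planned after 50 and 150 subjects complete the 6-week assessment for the primary outcome". If neither look crosses its boundary, enrolment continues and "the final analysis will be performed when all 236 subjects complete the study".

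The interim critical P values are "≤.0002 for the first analysis and ≤.012 for the second analysis", and the final analysis uses a critical P "value of ≤.0475". On their origin the section states: "These boundaries are obtained using O’Brien–Fleming spending function and based on an overall significance level of 5" per cent.

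Section 2.4 makes that level two-sided and gives the power target: "to achieve 80% statistical power at 5% (2-sided) level of significance". The planning difference is 10 points on the RSQ-W total score, with an SD of 25 and 15% drop-out.

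**The concern.** An O'Brien–Fleming spending function ties each critical value to the fraction of the total information available at that look. The looks here are not equally spaced: 50, 150 and 236 subjects are about 21%, 64% and 100% of the maximum. A P value of .0002 is far too generous for a first look at 21% of the information under this function. It is the familiar value for a first look at one third.

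The final value of .0475 is also higher than expected once two earlier efficacy looks have been taken. If the values were not computed for this schedule, the overall 5% claim does not follow from them. These are the thresholds that decide whether the trial stops early and whether it is declared positive. They are printed in the protocol as definite numbers, so a later analysis plan cannot supply them as if they had been left open.

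**Working it through.** **Inputs.** From section 2.9: looks at 50, 150 and 236 subjects; critical P values .0002, .012 and .0475; overall level 5%. From section 2.4: two-sided testing, difference 10, SD 25, drop-out 15%. A constant drop-out proportion cancels from the information fractions.

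**Information fractions.** 50/236 = 0.212, 150/236 = 0.636, 236/236 = 1.

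**Stated values as z limits.** |z| = 3.719, 2.512 and 1.982.

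**1. Can the plan's own figures be reproduced?** The O'Brien–Fleming-type spending function at .025 per tail is α(t) = 4[1 − Φ(2.2414/√t)]. At equally spaced looks (t = 1/3, 2/3, 1), solving for the boundaries gives z = 3.710, 2.511, 1.993, that is P = .0002, .0120, .0463. The first two stated values are reproduced; the final .0475 is not.

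**2. The same function at the actual looks.** Cumulative alpha is .0000022, .0099 and .0500. The boundaries are z = 4.731, 2.581 and 1.987.

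**3. Other readings of the O'Brien–Fleming label**, in case a different form was meant. All rows are two-sided P values at t = 0.212, 0.636, 1:

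| Form | Look 1 (50) | Look 2 (150) | Final (236) |
|---|---|---|---|
| Stated in section 2.9 | .0002 | .012 | .0475 |
| Spending function, .025 per tail | .0000022 | .0099 | .0469 |
| Spending function, two-sided .05 | .00002 | .0139 | .0448 |
| Classical O'Brien–Fleming, z = 1.998/√t | .000014 | .0122 | .0457 |

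No form yields .0002 at the first look. The stated value is larger by a factor of .0002/.0000022 ≈ 91, .0002/.00002 = 10 and .0002/.000014 ≈ 14 respectively. No form yields a final value as high as .0475.

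**4. Overall type I error of the stated set.** The probability, under no effect, of first crossing at each look was computed by recursive numerical integration for a process with independent increments:

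- look 1: .0002
- look 2, not having crossed before: .0119
- final, not having crossed before: .0395
- total: .0002 + .0119 + .0395 = .0516

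A simulation with 4 million replicates also gives .0516. Taking all three P values at the low or high end of their rounding gives .0513 to .0520, so rounding does not explain the excess. At equally spaced looks the stated set would still spend .0512. Adding the three nominal P values (.0597) is not the right measure, because the test statistics at successive looks are correlated.

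**5. Which value causes the excess?** Keeping .0002 and .012 at the actual fractions and solving for the final value that gives exactly .0500 yields P = .0457. Lowering the final value alone is therefore enough to restore 5%.

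**6. Power at 236 subjects.** With 15% drop-out, 236 × 0.85 = 200.6 subjects are evaluable, and the expected final z is 10/(25·√(4/200.6)) = 2.83. Group-sequential power is 80.7% with the stated values, 80.4% with .0000022/.0099/.0469, and 80.3% with .0002/.012/.0457.

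**The case against.** The strongest counter-argument is that the consequence is small. The excess is 0.16 percentage points, and relative to the set that keeps .0002 and .012, the final decision changes only for a P value between about .0457 and .0475. The first look spends only .0002, so its leniency adds almost nothing to the overall error. All of this is correct. It limits the size of the problem but does not make the stated claim true.

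Second, the article does not say which form of the spending function was used. The first-look discrepancy is therefore 10-fold to about 90-fold depending on the form, and .012 at the second look is too lenient under one form, slightly strict under another and close to the classical value. This also stands as a caution. However, the stated .0002 and .012 match the per-tail form exactly at equal spacing, which makes that form the natural reference. Under every form the set as a whole fails.

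Third, section 2.9 allows the DMC to stop for futility, which can only lower the realised error. Because such stopping is discretionary, planned error control cannot rely on it.

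Finally, the source of .0475 is unknown. It resembles .0457 with two digits exchanged, but the document cannot settle that, and the finding does not depend on it.

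**Conclusion.** The concern holds. At looks of 50, 150 and 236 subjects the printed critical values are not O'Brien–Fleming boundaries in any of the forms tried, and their overall two-sided type I error is 5.16% against the claimed 5%. The two interim values appear to come from a calculation for equally spaced looks, which this trial does not have; the final value fits neither schedule.

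The inflation is modest and is driven by the final .0475. The first-look threshold is the value furthest from the named method. The result assumes information proportional to the number of subjects, the same drop-out proportion at each look, and no credit for futility stopping. It should be corrected before any look is taken, because these numbers are the decision rule and the stated error control is not achieved.

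**What to change.** Replace the three values in section 2.9 by a set computed at fractions 0.212, 0.636 and 1. Either of these holds two-sided 5%:

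- **Keep the named method.** State the O'Brien–Fleming-type spending function at .025 per tail and use P ≤ .0000022, .0099 and .0469.
- **Keep the interim values.** Retain .0002 and .012, set the final value at .0457, and no longer describe the set as coming from an O'Brien–Fleming spending function.

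The mean differences that section 2.9 quotes for early stopping depend on the interim values and need updating if those change. It would also help to say that the boundaries will be recomputed from the number actually evaluable at each look, since the counts may differ from 50, 150 and 236. The correction itself does not depend on that addition.

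The cost is a change of wording and numbers. Power at 236 subjects falls from 80.7% to 80.4% with the first option or 80.3% with the second, which still meets the 80% target. No additional subjects are needed.

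### The first-look stopping difference of 26 points does not reach the stated critical P of .0002 under the stated SD of 25 and 15% drop-out, and the 12 points at the second look is not on the same basis.

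*Protocol article*

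**What the plan says.** Section 2.9 puts all the inputs in one place. Timing: "Interim analyses for efficacy are planned after 50 and 150 subjects complete the 6-week assessment for the primary outcome (or discontinue the study", so a subject who drops out counts toward the 50 or the 150. Critical P values: "≤.0002 for the first analysis and ≤.012 for the second analysis". As the equivalent in points, it says stopping for efficacy is likely "if the observed mean difference between the study treatment groups is at least 26 points and 12 points, respectively". The assumptions given for that translation are "assuming SD = 25 points, and drop-out rate = 15" per cent.

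Section 2.4 supplies the rest: equal allocation ("The planned sample size of 150 subjects (75 in each study treatment group") and a two-sided test ("to achieve 80% statistical power at 5% (2-sided) level of significance").

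**The concern.** The point differences are offered as a restatement of the P-value boundaries, so each should follow from its critical P, the SD and the number of subjects with data. The first does not: an observed 26 points would leave P above the boundary.

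This is the figure that tells a reader, or the Data Monitoring Committee, how large an effect would end the trial early. As printed, it makes the first boundary look easier to reach than it is. For observed differences between 26 and roughly 28.5 to 31 points, the two descriptions of the boundary in section 2.9 disagree.

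**Working it through.** **Inputs.** Looks at 50 and 150 subjects, critical P .0002 and .012, SD 25, drop-out 15% (section 2.9). Allocation 1:1 and two-sided testing (section 2.4).

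**Check that the inputs fit the plan.** For a 10-point difference at 80% power, n per arm = 2 × 25² × (1.960 + 0.842)² / 10² = 98.1, so 99. Then 99 / 0.85 = 116.5, so 117 per arm and 234 in total. That is close to the 236 subjects of the final analysis ("The final analysis will be performed when all 236 subjects complete the study"), so an SD of 25 and division by 0.85 are consistent with the document.

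**Formula.** Critical difference = critical value × SE, with SE = 25 × √(2/n) and n the number analysed per arm.

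**Trying to reproduce 26 points without drop-out.** n = 25 and SE = 25 × √(2/25) = 7.071. The two-sided normal critical value for .0002 is 3.719, so the difference is 3.719 × 7.071 = 26.3. An observed 26 gives z = 3.677 and P = .00024, still just above .0002. With a t-test the difference is 28.5.

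**First look with the stated 15% drop-out.** n = 25 × 0.85 = 21.25 and SE = 25 × √(2/21.25) = 7.67.
- Normal: 3.719 × 7.67 = 28.5 points.
- t (40.5 df): 31.4 points.
- An observed 26 gives 26 / 7.67 = 3.39, so P = .0007 (normal) or .0016 (t). That is about 3 to 8 times the boundary.

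**Second look with 15% drop-out.** n = 75 × 0.85 = 63.75 and SE = 25 × √(2/63.75) = 4.43. The normal critical value for .012 is 2.512.
- Normal: 2.512 × 4.43 = 11.1 points.
- t: 11.3 points.
- An observed 12 gives 12 / 4.43 = 2.71, so P = .0067 (normal) or .0077 (t). This crosses .012.

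**Other readings at the stated critical P values:**

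| Reading | First look, normal / t | Second look, normal / t |
|---|---|---|
| 15% drop-out, N × 0.85 | 28.5 / 31.4 | 11.1 / 11.3 |
| 15% drop-out, whole subjects (21 and 63 per arm) | 28.7 / 31.6 | 11.2 / 11.4 |
| Drop-out as N / 1.15 | 28.2 / 30.9 | 11.0 / 11.2 |
| No drop-out | 26.3 / 28.5 | 10.3 / 10.4 |
| One-sided P, 15% drop-out | 27.2 / 29.6 | 10.0 / 10.1 |
| Stated in section 2.9 | 26 | 12 |

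No row gives both stated figures. Working backwards with the normal formula, 26 needs about 51 analysed subjects, more than the 50 at that look, and 12 needs about 110 of 150 (27% drop-out). At 15% drop-out, 26 implies an SD of 22.8 and 12 implies an SD of 27.0.

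A different first boundary, P of about .0007, would give 26.0 points with drop-out. That is not the boundary the protocol states. The origin of the 26 cannot be settled from the document.

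**The case against.** The strongest reply is that the P values are the rule and the points only illustrate it. Section 2.9 sets a critical P for each look and calls stopping merely likely at the given differences. The real test will use the observed SD: at the first look, 26 points would cross .0002 if that SD were about 22.8 or less (normal) or 20.7 or less (t). This stands as far as error control goes. It does not rescue the figure, because the sentence fixes the SD at 25 and the drop-out at 15%, and under those values 26 fails.

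A reader might infer that both figures are wrong in the same way, so that at the second look the trial would wrongly continue for differences between 11.3 and 12 points. The document does not support that. It gives 12 as a difference that is enough to stop, and 12 is enough. It does not say that smaller differences mean continuing, and 12 is the next whole point above 11.1 or 11.3. What remains is that rounding up cannot also turn 28.5 into 26, so the two figures do not share a basis.

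A reader might also infer that the committee would stop on 26 points against the P-value rule. No charter is shown, and section 2.8 says the members have a statistical background, so this is only a possibility. The affected range is also seldom reached: with SE 7.67, an observed difference between 26 and 28.5 has a chance of about 1.1% if the true difference is 10 points and 3.7% if it is 15. Up to 31.4 points, the chances are about 1.6% and 6%.

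Finally, section 3.7 names only standard tests, so neither 28.5 nor 31.4 can be called the one correct replacement until the test is named.

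**Conclusion.** The point holds for the first look. Under section 2.9's own assumptions, 26 points does not meet P ≤ .0002. The stated difference is too low by about 2.5 points (28.5 − 26, normal) or 5.4 points (31.4 − 26, t). The second figure is true as a sufficient value, but it lies 0.7 to 0.9 points above its threshold and is not computed on the basis of the first.

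This rests on two-sided P values, equal arms, an unadjusted comparison of means, and discontinued subjects contributing no data. It takes the critical P values as given; whether they suit the planned timing of the looks is a separate question. Type I error is unaffected if the P values are applied. The error lies in what readers and the committee are told to expect, which makes it worth correcting but not a flaw in the decision rule.

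**What to change.** In section 2.9:
- Replace 26 by about 28.5 points (normal) or 31.4 points (t), and name the test used.
- Give the second figure on the same basis: about 11.1 points (normal) or 11.3 (t). If whole points are preferred, say that the values are rounded up.
- State that the critical P value, not the point difference, is the stopping rule.
- If the critical P values are ever revised, recompute both differences from them.

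The cost is one or two sentences in section 2.9, plus the same figures in any committee charter that repeats them. The sample size, the boundaries and the trial's conduct do not change.
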